**Fig. 1 Fig1:**
[figure not shown]
Schematic of Study Design

Scientific rigor will characterize the analysis of all quantitative and qualitative data. Assessments and focus groups will be implemented by trained research personnel to assure that responses are acquired consistently and will utilize written materials that can be used by future researchers. To ensure reproducibility, we will use sensitive and reliable measures and recruit a large and diverse sample that will provide sufficient statistical power to be likely to reflect a representative sample of couples coping with aging and cognitive decline.

### Eligibility requirements

To be eligible, participants must be spouses or partners who are living together in the community at the time of enrollment. Both must be willing to participate in the intake and follow-up assessments. They must be English-speaking adults aged 65 years or older. All participants must have internet access and a device that is compatible with a HIPPA-compliant video teleconferencing application in order to be able to participate in the interviews that will be conducted via videoconference. All participants must be able to complete the informed consent process. The study will exclude anyone who is deemed not to have capacity to consent, those with a prior diagnosis of schizophrenia or other psychotic disorder or with a prior diagnosis of a chronic disabling medical condition that would make it impossible to participate in virtual study visits. Those who participate in the focus groups must be willing to have their comments recorded.

### Recruitment

Participants will be recruited from the NIH-funded Alzheimer’s Disease Research Center ([name], Psychosocial Core Leader), the New York State-funded NYU Alzheimer’s Disease and Related Dementias Family Support Program ([name], Director), the Boston University Alzheimer’s Disease Research Center ([name], Research Education Core Leader), The Bedford VA Hospital Memory Diagnostic Clinic ([name], Director), and the Alzheimer’s Family Support Center, Cape Cod, MA as well as from registers of people interested in participating in research about aging and cognitive decline such as the Banner Health Alzheimer’s Prevention Registry. These facilities collectively serve more than 1000 participants age 65 and older each year. Additional participants will be recruited via newspaper ads and social media. Efforts will be made to ensure enrollment of participants from a wide range of socioeconomic and ethnic backgrounds.

The research coordinators will answer calls about the study and administer a structured screening questionnaire virtually via a HIPPA-compliant videoconferencing platform that will include background information and initial eligibility criteria. Prospective participants, who appear to be eligible based upon the initial screen, will be invited to join the study, asked to sign an electronic informed consent and then will be scheduled for a virtual intake assessment. At baseline, the interviewer will review the protocol with the potential participants and answer any questions. Our experience in prior studies suggests that recruitment and retention will be enhanced by giving participants a sense that their efforts are valued. To do so, we will provide a small monetary compensation for completing the assessments. We will invite all participants to an annual colloquium which can be attended in person or via live streaming, at which time we will share information on the progress of the study. Participants will also be offered individual feedback in an interactive session with a study clinician after their last assessment; they will receive a written summary of their personal and relationship characteristics, based on their responses to our assessment.

### Assessment

#### Process

Assessments will be conducted via videoconferencing, using a HIPPA-compliant video-conferencing platform. Each participant will complete the assessments separately from his or her partner. The assessments will be administered by a research coordinator verbally, with visual cues shared on screen for certain instruments when necessary. The assessment process will be consistent and standardized at both sites and for all interviewers. We anticipate that it will take couples an average of 2 h at baseline and 1.5 h at follow-up to complete the assessments, based on the results of a pilot of the battery with eight older individuals who completed it in as little as 40 min and no more than 1 h.

We will collect data from each member of the couple that includes demographic characteristics, psychosocial attributes (e.g., perceived social support, self-efficacy), relationship factors (relationship satisfaction, relationship continuity, partnership approach) and outcomes, including global quality of life, physical health, mental health (depression and anxiety) and status change (for example, placement outside the home). This assessment battery will enable us to estimate the contribution of relationship factors, above and beyond the commonly well-studied individual factors, to caregiver and care-recipient outcomes.

For couples in which one participant identifies as the caregiver of the other, we will use additional instruments to measure caregiver responses to the effects of cognitive changes (e.g., loss of intimate exchange, ability to identify positive aspects of caregiving) and care-recipient attributes (i.e., functional ability and behavioral problems from the perspective of the caregiver). It should be noted that, if one member of the couple declines in cognitive function and the other doesn’t identify as a caregiver, the caregiver battery will not be used.

At each follow-up visit, the same procedure used during the intake visit will be followed. As the individuals with cognitive impairment or ADRD progress in the severity of their symptoms, they will continue in the study until scoring 12 or less on the MoCA or are deemed to lack capacity, after which they will be withdrawn from the study; their study partner will continue to participate.

If scores on any of the measures in the assessment indicate a participant may have had a significant change in cognition or emotional status, we will notify both members of the dyad, and we will provide the opportunity to discuss these results with a study clinician and receive appropriate referrals.

#### Assessment battery

The measures selected for this study were chosen to enable us to fulfill our Specific Aims. Many of these scales are included in the NIH toolbox.

All study participants will complete the following assessment battery at baseline:

Demographic questions, including age, gender, race/ethnicity, socio-economic status, characteristics of marriage (years married, first marriage?), number of children, work history (ever worked, currently working). Demographic questions will be administered only at baseline.

Cultural expectations of marriage (traditional/nontraditional) –One item: “How traditional do you consider your marriage, on a scale of 0 to 10, where 0 is nontraditional and 10 is very traditional?”

Attachment Questionnaire [23]: This 3-item questionnaire focusing on three distinct attachment styles; secure attachment, Anxious/Ambivalent attachment, and Avoidant attachment each rated on a 7-point Likert scale with “1= Strongly disagree” and “7= Strongly agree”. The Attachment Questionnaire will only be administered at baseline, as it is considered to be a stable attribute for the purpose of this study.

Revised Dyadic Adjustment Scale [24]: This 14-item scale designed to measure relationship satisfaction in three domains: 1) Dyadic Consensus, 2) Dyadic Satisfaction, and 3) Dyadic Cohesion.

Partnership Approach Questionnaire [25]: This 28-item scale assesses respondent’s caregiving style; whether the caregiver employs an individual-based caregiving style or views the couple as a team working towards the caregiving needs placed upon them. Rated on a 7-point Likert scale with “1= completely disagree” and “7= completely agree”.

Measures of family style (SCORE) [26]: This 15-item questionnaire measures the quality of the respondent’s family life. Rated on a 5-point Likert Scale with “1= describes us: very well” and “5= describes us: not at all”.

Lubben Social Network Scale-6-Item Version [27]: This 6-item questionnaire measures the number of family members and friends they hear from once a month, free close to, and feel at ease with discussing private matters, to get an overall understanding of their social support network.

Social Support availability [28]: This measure includes three 4-item subscales of emotional, instrumental and informational support.

Loneliness [29]: Measures feelings of loneliness, whether or not one has a large social network.

Life Orientation [30]: This 10-item assessment of feelings of generalized optimism vs pessimism, rated on a 5-point scale ranging from “I agree a lot” to “I disagree a lot”.

Meaning and Purpose in Life [31]: This 18-item measure of life purpose rated on a 5-point Likert scale from Strongly Disagree to Strongly Agree.

Coping self-efficacy [32]: This 10-item questionnaire assessing feeling of self-efficacy in daily activities, rated on a 5-point Likert scale with “1 = Never” and “5= Very Often”.

Geriatric Depression Scale [33]: This 15-item measure of symptoms of depression among older adults; 15 ‘yes’ or ‘no’ questions in which participants respond in reference to how they felt over the past week.

Beck Anxiety Inventory (BAI) [34]: This 21-item measure of symptoms of anxiety during the past month on a 4-point scale from “Not at all” to “Severely-it bothered me a lot.”

Physical Health Questionnaire [35]: This measure includes three global self-rated physical health items from the OARS battery of questionnaires (ICC = 0.83) to assess subjective evaluation of health The sum of the 3 questions is used to measure SRH.

Sleep Survey: This measure includes two items to assess subjective sleep quality over the previous month.

EuroQol Questionnaire Global Quality of Life [36]: This measure assesses overall quality of life on a scale of 0–100 with “100 being the best quality of life imaginable”.

Caregiver Screener: Once all of the above questionnaires are completed, all individuals will be administered a short Caregiver Screener which asks if individuals identify as a caregiver, if their care partner needs additional help with tasks, how often they provide care, and utilization of outside resources to assist in caring for their partner. The screener determines whether additional questionnaires should be implemented with the caregiving partner.

*Functional Activities Questionnaire [22]: This 10-item measure to assess the abilities of the person with dementia. Each functional activity assessed as: (3) Dependent; (2) Requires assistance; (1) Has difficulty but does by self; (0) Normal or (0) Never did [the activity] but could do now; (1) Never did and would have difficulty now.

*Revised Memory and Behavior Checklist [37]: This 24-item measure assesses the functioning and behavior of an individual with dementia. Caregivers are asked if a certain behavior is present and if so how much it bothers them, on a scale from “Not at all” to “Extremely.”

*Service Utilization: Scale about utilization of different support services, including respite care, support groups, food services, etc.

*Birmingham Relationship Continuity Measure [38]: This 23-item scale assessing caregiver’s appraisal of relationship continuity, their negative and positive emotional reactions to the caregiving role; rated on a 5-point Likert scale ranging from “Agree a lot” to “Disagree a lot”.

*Deprivation of Intimate Exchange [15]: How much have you lost?: (a) Being able to confide in your (relative); (b) The person that you used to know; (c) having someone who really knew you well. Response categories: (4) completely; (3) quite a bit; (2) somewhat; (1) not at all.

*Positive Aspects of Caregiving Scale [39]: This 9-item assess caregivers’ perceptions regarding the positive aspects of caregiving; two components, (1) self-affirmation and (2) outlook on life rated on a 1–5 Likert scale with “1= disagree a lot” and “5= agree a lot” .

Montreal Cognitive Assessment (MoCA) [21] will be administered to all participants at the end of each interview. The MoCA is a screening instrument that assesses multiple cognitive domains: attention and concentration, executive functions, memory, language, visuospatial skills, conceptual thinking, calculations, and orientation.

Status Change Form, indicating the type and date of transitions, such as residential care placement, illness, move, refusal and death will be filled out when the participant informs the study personnel of the change, which may be during an ad hoc call, a scheduling call, or a follow-up assessment.

The questionnaires listed above, except for demographics, cultural expectations of marriage, and the Attachment Questionnaire, will be administered at all of the follow-up visits, unless a change in living arrangements or death of one member of the couple occurs, when the procedure will be altered to suit the new circumstances:
Change in Living Arrangements: If the living arrangements for the couple change during study participation, adjustments will be made to the assessment schedule to adjust for the changes in interaction and caregiving responsibilities. Visits will continue at regular intervals for both individuals if cognitively capable of consenting. All measures, except for the Revised Memory and Behavior Checklist (if caregiver), will be administered.Bereavement: Should one member of the couple die, the other individual will be asked to complete an exit bereavement assessment 6 months after the date of death, which will include the following measures from the main assessment battery: Dyadic Adjustment Scale, SCORE Measures of Family Style, Lubben Social Network Scale, Social Support Availability, Loneliness, Life Orientation, Meaning & Purpose in Life, Coping Self-Efficacy, Geriatric Depression Scale, Suicidality Evaluation, Beck Anxiety Inventory, Physical Health Questionnaire, and EuroQoL. In addition to these measures, the Texas Revised Inventory for Grief [40] will be administered during this assessment.

Texas Revised Inventory of Grief-Present [40]: This 13-item measure assess an individual’s present feelings of grief, rated on a scale from “1 = completely true” to “5 = completely false”.

##### Sample size calculation

Sample size was based upon the proposed longitudinal analysis investigating the effect of clinical group and relationship characteristics on changes in the primary outcomes over time. With an initial sample size of 300 couples (600 individual participants) and a potential dropout rate of 20% per group, we have powered the analysis to provide useful outcomes with a sample size of 240 dyads [41]. We have calculated the necessary sample size to sufficiently power the analyses for the smallest clinically substantive effect on the outcomes using the Geriatric Depression Scale scores in each of our three groups (cognitively normal controls, MCI, and AD). We made the following assumptions: 1) the minimum detectable effect size is 0.20, 2) there is 1 baseline measurement and either 3 or 5 post-baseline measurements, 3) two-tailed alpha error is 0.05, 4) power was set 0.8, and 5) the within-person association for over-time measurement is 0.7. With these assumptions, the study will need 50 patients for 3 follow-up measurements and 48 patients for 5 follow-up measurements per clinical group to adequately investigate the primary outcome, Geriatric Depression Scale scores [42]. The addition of covariates as well as multiple predictor variables and attrition will necessarily reduce this power; therefore, we have increased the sample size for those groups that may suffer most from attrition and offer the most clinical relevance (MCI and AD). Also, we will use model-building techniques (e.g., backward elimination) to fit the most parsimonious models. The use of sensitive and reliable measures and employing mixed-effects models to analyze repeated measures, which preserve all available data, will also, in general, improve power [43]. Lastly, the use of continuous predictor variables when available, e.g., MoCA score should also increase power over the use of categorical variables. With a sample of 300 couples at baseline, we are well powered to conduct the proposed analyses.

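### The effect size of 0.20 has no stated metric and does not yield 50 and 48 per group; a two-group time-averaged difference of 0.50 SD does

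*Protocol article*

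**What the plan says.** All the inputs and the result stand in the protocol article, under Sample size calculation. The inputs are that "the minimum detectable effect size is 0.20"; that "there is 1 baseline measurement and either 3 or 5 post-baseline measurements"; that "two-tailed alpha error is 0.05"; that "power was set 0.8"; and that "the within-person association for over-time measurement is 0.7". The section presents its result as following from these: "the study will need 50 patients for 3 follow-up measurements and 48 patients for 5 follow-up measurements per clinical group", in order "to adequately investigate the primary outcome, Geriatric Depression Scale scores". It describes the target as the smallest effect of clinical substance on that scale, allows for 20% dropout per group (300 dyads falling to 240), and closes: "With a sample of 300 couples at baseline, we are well powered to conduct the proposed analyses".

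The Methods overview plans 60 dyads with normal cognition, 140 with MCI and 100 with early ADRD. The plan for Aim 2 specifies repeated measures models with a group by time interaction, adjusted for baseline variables.

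**The concern.** Inputs and output are both printed, and the second is said to follow from the first, so the step can be checked. An effect of 0.20 is small if it is in SD units, and about 50 per group is far too few to detect a difference of that size between two groups. The section never names the metric or the test, so the reader cannot tell which of the figures is wrong.

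At stake is what the study can claim about its sensitivity. If 0.20 is a standardised mean difference, the text promises 80% power for an effect that the retained sample would often miss. A reader who took the section at face value could then give too much weight to a non-significant group difference in depression scores.

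**Working it through.** **Inputs.** From Sample size calculation: effect 0.20; two-sided alpha 0.05 (z = 1.960); power 0.80 (z = 0.842); correlation ρ = 0.7; m = 3 or 5 post-baseline measures; 20% dropout. From the Methods overview: 60/140/100 dyads enrolled, so 48/112/80 after dropout (0.8 × 60, 0.8 × 140, 0.8 × 100; sum 240). Follow-up every 6 months for 3 years gives six visits, so m = 6 is shown where useful. Assumptions: outcome SD set to 1, one patient counted per dyad.

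**1. Reproducing 50 and 48.** For two groups compared on the mean of m equally correlated measures:

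n per group = 2(1.960 + 0.842)² × V / d², with V = [1 + (m − 1)ρ]/m

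- 2(1.960 + 0.842)² = 15.70
- V = 0.80 (m = 3), 0.76 (m = 5), 0.75 (m = 6)
- d = 0.50: 15.70 × 0.80 / 0.25 = 50.2; 15.70 × 0.76 / 0.25 = 47.7
- Solving back from 50 and 48: d = 0.501 and 0.499

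One round effect size returns both printed figures with the document's own alpha, power, correlation and visit counts. For two equal groups, d = 0.50 is f = 0.25.

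**2. The stated 0.20 under the same formula.** 15.70 × 0.80 / 0.04 = 314; 15.70 × 0.76 / 0.04 = 298. At 50 or 48 per group, power for 0.20 SD is about 20%.

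**3. Other readings of 0.20.** Patients per group:

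| Reading | m = 3 | m = 5 |
|---|---|---|
| Time-averaged mean, AR(1) correlation | 296 | 242 |
| Mean including baseline | 304 | 294 |
| Change from baseline, V + 1 − 2ρ | 157 | 141 |
| Full baseline adjustment, V − ρ² | 122 | 106 |
| Time-averaged mean, one-sided | 247 | 235 |
| Slope difference totalling 0.20 SD | 212 | 168 |
| Slope difference of 0.20 SD per visit | 24 | 7 |
| Cohen's f, two groups, time-averaged | 80 | 76 |
| Cohen's f, three groups, time-averaged | 66 | 63 |
| Cohen's f, group by time test, 2 or 3 groups | 11-13 | 8-10 |

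None gives the pair 50 and 48.

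**4. Power if 0.20 is in SD units.** SE = √{variance × (1/n₁ + 1/n₂)}; power ≈ Φ(0.20/SE − 1.960); detectable difference = 2.802 × SE. The ranges cover m = 3 to 6.

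| Contrast, retained sizes | Power, unadjusted | Detectable SD | Power, fully baseline-adjusted | Detectable SD |
|---|---|---|---|---|
| Normal v MCI (48 v 112) | 25-27% | 0.42-0.43 | 55-62% | 0.25-0.27 |
| Normal v ADRD (48 v 80) | 23-24% | 0.44-0.46 | 50-58% | 0.26-0.29 |
| MCI v ADRD (112 v 80) | 33-35% | 0.36-0.37 | 69-76% | 0.21-0.23 |

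Worked case, normal v ADRD, m = 3, unadjusted: SE = √{0.80 × (1/48 + 1/80)} = 0.163; 0.20/0.163 − 1.960 = −0.73; power 23%; detectable difference 2.802 × 0.163 = 0.46.

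At the enrolled 60/140/100, unadjusted power is 28-42%. With full baseline adjustment it is 60-85%, and only MCI v ADRD passes 80% (84% at m = 5).

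**5. Power if 0.20 is Cohen's f in a three-group test of time-averaged means.** With noncentrality N f²/V, N = 240 gives 88% (m = 3) to 90% (m = 6). At the printed 50 (m = 3) or 48 (m = 5) per group, power is 68%.

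**The case against.** The strongest reply is that the metric is open. On the f scale the figure that fits is 0.25, close to the printed 0.20, and a three-group test at f = 0.20 has about 88-90% power with 240 dyads. This stands. On that reading the closing claim of adequate power survives for that test, although 50 and 48 per group remain wrong.

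The second reply is that Aim 2 adjusts for baseline and the sample size section counts a baseline measurement, so the unadjusted formula understates power. This also stands. Full adjustment roughly doubles the power for 0.20 SD at retained sizes, but no contrast reaches 80%.

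Third, 48/112/80 are the sizes after dropout, not the planned ones, and mixed models keep partial data from dropouts. That is fair, so figures for enrolled sizes are given too. The retained sizes are nonetheless the 240-dyad basis that the document says it used. In the other direction, the section concedes that covariates, extra predictors and attrition cost power.

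A reader might infer that true power is 23-35% rather than 80%, or that the stated effect is simply 2.5 times too small. The documents do not support either without conditions: both hold only for an unadjusted two-group difference in SD units, and the percentages only at retained sizes. Nor does any document say that a null result will be read as excluding an effect of 0.20, so that harm is a possibility and not part of the plan.

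**Conclusion.** The inconsistency holds under every reading tried: the listed assumptions do not give 50 and 48 per group, while 0.50 SD (f = 0.25) in a two-group comparison of time-averaged means does. That 0.50 was the value actually used is an inference from the close match; the document does not say so.

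The size of the consequence depends on the missing metric. In SD units, 80% power for 0.20 is not met for any pair of groups at retained sizes, with or without baseline adjustment. As Cohen's f in a three-group test, the per-group requirement is understated by 16 and 15 patients (66 − 50, 63 − 48), but the total sample is adequate for that test. These figures rest on equal correlation of 0.7 between all visits, one patient per dyad, and 20% dropout in each group. Counting both partners as independent observations, the most favourable case, raises unadjusted power for 0.20 SD only to about 41-61% at retained sizes.

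**What to change.** In the sample size section:

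1. Name the effect-size metric and the test it serves.
2. Make effect and sample size agree. Either state that 50 and 48 per group give 80% power for a 0.50 SD time-averaged difference between two groups, or keep 0.20 and report the n and power that follow from it under the named metric and test.
3. State the effect detectable with 80% power at 48/112/80 for the named analysis: for pairwise time-averaged comparisons, about 0.36-0.46 SD unadjusted or about 0.21-0.29 SD with full baseline adjustment at correlation 0.7. If the group by time interaction is the test meant, give the figure for that test instead.
4. Withdraw the claim that 50 or 48 per group gives 80% power for 0.20, and tie the closing statement on power to the named analysis.

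The cost is rewording and one recalculation. Enrolment, visits and measures stay as they are. In SD units the stated sensitivity will look less favourable than it does now.
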